### Patient identification and data collection

Patients will be screened for inclusion criteria by the local team. Data collection will be carried out using the case report form presented in the online supplementary appendix A. Hospital or National Health Service (NHS) number will not be entered into this form but will be kept separately with a key sheet.

10.1136/bmjopen-2017-017928.supp1Supplementary data

Basic demographics, comorbidities and polypharmacy data will be recorded. Comorbidities will be collected based on the Charlson Comorbidity Index, a validated measure of prognostic impact of multiple chronic illnesses.^11^ This will allow for standardisation of comparisons between any groups. Data will also be collected on baseline independence status, assessed by the number of times social services provide care (1–4 times), and living in a residential or nursing home, measured both predischarge and postdischarge.

Frailty will be measured using the Clinical Frailty Score (online supplementary appendix B). This has been validated for use to assess frailty in older patients who underwent general surgery and OPSOC has successfully applied this before in previous work in this area.^12^ The score ranks from 1 to 7 with a score of ≥5 being classed as frail.

Data will be collected on preoperative risk from scoring systems used commonly within emergency general surgery. This will include the P-POSSUM score^13^ and the American Society of Anaesthesiologist grade.^14^

Data will be collected on operative procedures performed. Information will be obtained from patient case notes on 30-day outcomes. This includes 30-day mortality and evidence of postoperative complications. These complications will be rated using the Clavien-Dindo classification (online supplementary appendix C). This will allow for complications to be rated and outcomes to be assessed together. Finally, information will be obtained from the patient notes regarding 90-day mortality.

A detailed summary of the study questions asked can be found in the online supplementary appendix A.

The timetable for data collection is given in table 1.

**Table 1 T1:** Timetable for data collection

Period	Date
Case identification period	20/03/2017 - 19/06/2017
Data collection completion date	19/09/2017
Validation completion date	30/09/2017

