### Statistical analysis and power calculation

Using OPSOC data, frailty exists in 28% of older patients admitted with emergency surgical conditions. Fifty-four per cent of the frail people who underwent surgery had died after 90 days. In order to detect a 10% difference in mortality rate at day 90 between frail and non-frail patients, a sample size of 480 is required, given an expected mortality proportion in those not frail of 0.075 and those frail of 0.175 (data from OPSOC), assuming an 80% power. We anticipate minimal patients who are lost to follow-up and to account for this, we will aim to recruit 500 patients.

Statistical support will be provided by OPSOC. Data will be analysed for correlation between frailty and postoperative outcomes, including 90-day mortality, complications and loss of independence.

Our primary analysis will be a logistic regression of 90-day mortality by frailty, adjusted for age (65–74, and >75 years old) and gender. We will carry out a secondary analysis of the primary outcome by including additional clinical mediators which are determined statistically important using a likelihood ratio test with a stepwise model fitting approach of nested regression models, and presented as a final multivariable model. All analyses will be presented as adjusted OR with associated 95% CIs and p values.

All other outcomes will be analysed as per the above analysis, but will be deemed secondary outcomes.

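### The secondary multivariable model picks its covariates (called clinical mediators) by stepwise testing on about 50 expected deaths, so its frailty odds ratio can be biased and its nominal 95% CI can under-cover; the primary analysis is unaffected

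*Protocol article*

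**What the plan says.** All of this is in the protocol article, section *Statistical analysis and power calculation*, unless stated otherwise.

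- **Primary analysis:** a logistic model of 90-day mortality on frailty, with fixed adjustment for two age bands and gender. Nothing is selected.
- **Secondary analysis of the same outcome:** the model is extended by "including additional clinical mediators which are determined statistically important using a likelihood ratio test with a stepwise model fitting approach of nested regression models". The result is to be presented as the final multivariable model.
- **Reporting:** "All analyses will be presented as adjusted OR with associated 95% CIs and p values". No allowance for the selection step is mentioned.
- **Scope:** the remaining outcomes are to be analysed in the same way, as secondary outcomes.
- **Possible candidates:** the candidate list is not given. The section *Patient identification and data collection* says "Basic demographics, comorbidities and polypharmacy data will be recorded". It also lists the Charlson index, ASA grade, P-POSSUM, operative procedures and postoperative complications among the data collected.

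**The concern.** The sentence raises two separate problems.

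**Selection.** Variables are kept or dropped by significance in the same data that then supply the frailty odds ratio. With few deaths, a confounder of modest strength often fails the test and is left out, so its share of the association stays in the frailty odds ratio. The usual interval treats the chosen model as if it had been fixed beforehand.

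**The word mediators.** A mediator lies between frailty and death. Conditioning on it takes out the part of the association that runs through it, so the odds ratio no longer describes the whole association that the study aims to assess. As worded, the sentence does not restrict candidates to variables known before surgery.

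The primary model adjusts only for age band and gender. The secondary model is therefore the only stated one that could account for comorbidity or baseline risk. The Background says the results should support surgical decisions and consent, so a biased estimate with an overconfident interval would matter.

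**Working it through.** **Inputs from the protocol.** Frailty prevalence: "frailty exists in 28% of older patients admitted with emergency surgical conditions". Mortality: "given an expected mortality proportion in those not frail of 0.075 and those frail of 0.175". Power: "assuming an 80% power". Recruitment target: 500. The same paragraph also states "Fifty-four per cent of the frail people who underwent surgery had died after 90 days". The significance level for the sample size is not stated; I assume two-sided 5%, in line with the 95% CIs.

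**1. The plan's own figure.** The plan says "a sample size of 480 is required". With unpooled variance and a 72:28 split,

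N = (z₀.₉₇₅ + z₀.₈₀)² / 0.10² × [0.075×0.925/0.72 + 0.175×0.825/0.28] = 784.9 × (0.09635 + 0.51563) = 480.3.

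This reproduces 480, so these inputs are the ones the study was sized on.

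**2. Expected deaths.** N × (0.28 × frail risk + 0.72 × non-frail risk):

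- N=500: 500 × (0.28×0.175 + 0.72×0.075) = 500 × 0.103 = 51.5
- N=480: 480 × 0.103 = 49.4
- N=500 with 54% frail mortality: 500 × (0.28×0.54 + 0.054) = 500 × 0.2052 = 102.6

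**3. Coverage of the frailty interval.** The simulations used 500 patients, about 51 deaths unless stated, and forward likelihood-ratio selection at 5%. The number of candidates, their strength, their link with frailty and the entry rule are assumptions; the protocol gives none of them. Fixed means a pre-specified model without selection.

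| Setting | Runs | True OR | Stepwise OR | Stepwise coverage | Fixed coverage |
|---|---|---|---|---|---|
| A: 10 candidates, 6 with log-OR 0.25 per SD, shifted 0.4 SD in frail patients | 1,200 | 1.49 | 1.95 | 82% | 95% |
| A with 54% frail mortality (102 deaths) | 1,200 | 9.41 | 12.06 | 84% | 94% |
| A with candidates unrelated to frailty | 1,200 | 2.72 | 2.76 | 95% | 95% |
| B: 12 candidates, 6 weak confounders correlated with frailty | 300 | 1.80 | 2.29 | 86% | 94% |
| C: 12 candidates, 6 with log-OR 0.2 per SD, shift 0.4 SD | 400 | 1.80 | not recorded | 80% (88% with 20% entry) | not recorded |
| C with shift 0.2 SD | 400 | 1.80 | not recorded | 93% (95% with 20% entry) | not recorded |
| D: as B, tracking frailty strongly / weakly / not at all | not recorded | 1.80 | 2.29 when strong | 84% / 93% / 95% | 94–95% |

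One run with heavier confounding (600 replicates, true OR 1.60, age- and gender-adjusted OR 3.27) gave 77% against 96%. Simulation error is about √(0.86×0.14/300) = 2.0 points for B and √(0.823×0.177/1,200) = 1.1 points for A, too small to explain the gaps.

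**4. Narrow interval or displaced estimate?** In setting A the mean stepwise SE is 0.323 and the actual SD is 0.372, so the SE is 1 − 0.323/0.372 = 13% too small. Without bias, the interval would reach 1.96 × 0.323/0.372 = 1.70 SD each side, which covers 91%. The estimate is displaced by ln 1.95 − ln 1.49 = 0.27, or 0.27/0.372 = 0.72 SD. Coverage is then Φ(1.70−0.72) − Φ(−1.70−0.72) = 0.84 − 0.01 = 83%, close to the simulated 82%. So about 4 of the 13 points lost come from width and about 9 from displacement.

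**5. What the odds ratio means.** In setting A the age- and gender-adjusted OR is 2.63, the stepwise OR 1.95 and the OR given all six variables 1.49. If the six are confounders, 1.49 is the target and 1.95 is under-adjusted. If they are mediators, 2.63 is the whole association and 1.95 has lost part of it. Either way, the stepwise result matches neither quantity.

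**The case against.** The strongest reply has four parts.

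- **It is only a secondary analysis.** This stands. The primary model has fixed covariates and involves no selection. A reader might infer that the main result is compromised; the protocol does not support that.
- **Mediators may be loose wording for preoperative risk factors.** This is plausible. The Charlson index is collected to make comparisons fair, and ASA and P-POSSUM are described as preoperative risk. A reader might infer that complications or intensive care stay will be adjusted for, with collider bias as a result. No section names them as covariates, and *Secondary outcomes* lists them as outcomes. What remains is that the sentence permits such variables. The selection problem is the same under either meaning.
- **The size depends on assumptions.** This stands. A reader might infer that the interval must miss its 95% level, or that the odds ratio is bound to be too small. Neither follows. Coverage is close to nominal when candidates are weakly related or unrelated to frailty, and dropped confounders push the simulated odds ratio up, not down. Most of the coverage loss in setting A is displacement, not width.
- **About 50 deaths is not the only figure.** This also stands: 54% frail mortality gives about 103. Setting A still covers only 84% there, so the concern does not depend on which figure is right.

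The candidate list and entry threshold may sit in a fuller plan, and their absence is no finding. The method itself is stated here, though, and that is what is criticised.

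**Conclusion.** The point holds for the secondary multivariable model of 90-day mortality and, because the recipe is carried over, for the corresponding models of the other outcomes. Choosing covariates by significance and then quoting ordinary intervals can bias the frailty odds ratio and make its 95% CI under-cover. With strong tracking of frailty, coverage was about 80–86% under 5% entry, and lower in one more heavily confounded run. With no relation to frailty it was nominal. Comorbidity and risk scores could reasonably be expected to track frailty, and true mediators do so by definition, but the documents give no figure for how closely. The direction of the bias is not fixed. Separately, the word mediators is either a licence to adjust away part of the association or a misnomer, and needs correcting in both cases. This is a moderate defect that should be put right before analysis.

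**What to change.** - Replace the stepwise step with one pre-specified secondary model limited to variables known before surgery and already collected: frailty, age, gender and Charlson index.
- Add a separate fixed model with ASA grade and the P-POSSUM preoperative risk, labelled as the prognostic value of frailty beyond existing scores.
- Replace mediators with preoperative covariates, and state that no variable arising during or after surgery enters either model. Procedure type is left out for that reason, since the protocol records procedures performed. Indication is left out because the data-collection section does not list it.
- Code sparingly. With one term each, the first model has 4 parameters (51.5/4 = 12.9 deaths per parameter) and the second has 6 (51.5/6 = 8.6). If more terms are needed, use penalisation.
- Label any stepwise model that is kept as exploratory.
- Apply the same rule to the other outcomes.

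This changes wording only and needs no new data. The cost is that weak covariates stay in the model and the frailty interval is slightly wider: in setting A the mean SE was 0.351 for the fixed model against 0.323 for the stepwise one, and the wider figure was close to the actual SD of 0.358.

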### Secondary outcomes

Length of hospital stay (measured in days)Postoperative complications (yes/no and Clavien-Dindo grade of complication)

Change in level of independenceLength of stay on high dependency unit and intensive care unit (measured in days)Intermediate care stay on discharge (yes/no and duration of stay measured in length of days)30-day mortality30-day readmission

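### Three secondary outcomes are measured in days, but the plan gives every secondary outcome the logistic-regression, odds-ratio analysis and names no cut-point

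*Protocol article*

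**What the plan says.** The protocol article's section on statistical analysis and power calculation sets the main model: "Our primary analysis will be a logistic regression of 90-day mortality by frailty, adjusted for age", in two age bands, and gender. A stepwise multivariable version follows as a secondary analysis of the same outcome. That paragraph ends by fixing the effect measure: "All analyses will be presented as adjusted OR with associated 95% CIs and p values". The next sentence extends the approach to everything else: "All other outcomes will be analysed as per the above analysis, but will be deemed secondary outcomes".

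The section listing the secondary outcomes gives their scales. Hospital stay is "Length of hospital stay (measured in days"), and HDU/ICU stay is likewise in days. Intermediate care after discharge is recorded as "yes/no and duration of stay measured in length of days". Complications are recorded as "yes/no and Clavien-Dindo grade of complication". Thirty-day mortality and 30-day readmission are binary by nature. Change in level of independence is listed without a scale.

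No cut-point for any duration, and no ordinal, count or time-to-event model, appears in the document.

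**The concern.** A protocol may leave secondary models to the analysis plan, and silence here would be no fault. This text is not silent: it names one model and one effect measure and applies them to all other outcomes. An analysis plan that used a suitable model for days would depart from the protocol's wording. One that followed the wording would have to create a binary variable from each duration, at a threshold that someone still has to choose.

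Three things are at stake:

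- **Choice of threshold.** A cut chosen once the data are visible lets the reported frailty effect depend on that choice.
- **Information.** Reducing a duration to short or long discards the rest of the measurement.
- **Death.** A patient who dies in hospital soon after surgery has a short stay. A short/long split places that patient with those who recovered and went home quickly. If early death is more common in the frail, this pulls the estimated association between frailty and long stay downwards.

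Length of stay is not peripheral. It comes first among the secondary outcomes, and the Background names it among the outcomes that earlier work linked to frailty.

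**Working it through.** **1. The plan's own figure.** The one statistical figure to reproduce is the sample size of 480. The inputs are "an expected mortality proportion in those not frail of 0.075 and those frail of 0.175", 28% frail and 80% power. Two-sided 5% is assumed, because alpha is not stated. With unpooled variance:

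N = (1.960 + 0.842)² × [0.075 × 0.925 / 0.72 + 0.175 × 0.825 / 0.28] / 0.10²
= 7.849 × [0.0964 + 0.5156] / 0.01 = 480.3.

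This matches 480. It concerns the primary outcome only, and nothing below depends on it.

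**2. Outcome scale against prescribed analysis.**

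| Secondary outcome | Scale in the protocol | Binary logistic regression with OR, as written? |
|---|---|---|
| Hospital stay | Days | No, unless split |
| HDU/ICU stay | Days | No, unless split |
| Intermediate care, any | Yes/no | Yes |
| Intermediate care, duration | Days | No, unless split |
| Complications, any | Yes/no | Yes |
| Clavien-Dindo grade | Ordered | Not binary; ordinal logistic regression gives an OR but is not named |
| 30-day mortality | Yes/no | Yes |
| 30-day readmission | Yes/no | Yes |
| Change in independence | Not stated | Depends on the coding |

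The conflict is clear for three entries and is a matter of naming the model for Clavien-Dindo grade. A trial run on simulated data (500 patients, 28% frail) agreed: software refused a binary logit for a day count and for a 0–5 grade, while a proportional-odds model fitted the grade and returned an odds ratio.

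**3. Direction of the death problem.** Let d be the proportion of a group dying in hospital before the cut, and p the proportion with a long stay among the rest. The long-stay proportion in the whole group is p(1 − d). Suppose frailty has no effect on stay among the rest, so p is the same in both groups. The ratio of long-stay proportions, frail to non-frail, is then (1 − d_frail) / (1 − d_non-frail), whatever p is.

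The document gives no in-hospital death rates before any cut. As an illustration, assume that a fraction f of the planning 90-day deaths (0.175 and 0.075) occur in hospital before the cut, with the same f in both groups:

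- f = 0: ratio 1.00
- f = 0.5: (1 − 0.0875) / (1 − 0.0375) = 0.9125 / 0.9625 = 0.95
- f = 1: 0.825 / 0.925 = 0.89

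So a frailty effect of nil on stay would appear as up to about 11% fewer long stays in the frail. This shows the direction and a bound under these planning rates; it does not estimate what the study will find.

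**The case against.** The strongest reply is that the wording is loose rather than wrong. The odds-ratio sentence closes the paragraph on the primary outcome, so the sentence after it may mean only the same structure: frailty, adjusted for age and gender, then a stepwise model. This is a condensed article, its analysis plan is not shown, and nowhere does it say that days will be dichotomised. That reading is possible and is a reason for moderate severity. It does not remove the conflict, because the text says that all analyses will be odds ratios and that all other outcomes follow the analysis above.

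Some stronger readings are tempting but are not supported:

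- *None of the secondary outcomes can be analysed as stated.* The yes/no outcomes can. Clavien-Dindo grade can be handled within the logistic family and still yield an odds ratio.
- *About 35% of the information will be lost.* The efficiency of 2/π = 0.64 belongs to a median split of a normally distributed outcome. The plan states no median split, and stays are usually skewed, so this is not a figure for this study.
- *Odds ratios are wrong for the primary outcome.* Mortality is binary and logistic regression suits it. At the planning rates the odds ratio is (0.175/0.825) / (0.075/0.925) = 2.62 and the risk ratio is 0.175/0.075 = 2.33. Contrasting 54% with 44% would need a non-frail rate that the document does not give. Adjusted risk differences would be a useful extra, but their absence is not an error.

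**Conclusion.** The point holds for hospital stay, HDU/ICU stay and intermediate-care duration. The prescribed analysis does not fit their scale, and following it requires a cut-point that the plan does not supply. For Clavien-Dindo grade the gap is narrower: a suitable model exists within the stated effect measure and only needs naming.

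The practical effect cannot be sized from the document, because it depends on the cut chosen, the distribution of stays and the timing of in-hospital deaths. The direction of the death problem follows if early in-hospital death is more common in the frail. That is an assumption, though one consistent with the higher frail mortality in the study's own planning rates.

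The primary outcome, its model and the sample size are unaffected. This is a should-fix.

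**What to change.** Replace the sentence on other outcomes with a model and effect measure for each, using the same covariates throughout:

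- **Yes/no outcomes** (any complication, any intermediate care, 30-day mortality, 30-day readmission): logistic regression with adjusted odds ratios, as now.
- **Clavien-Dindo grade:** proportional-odds (ordinal logistic) regression with an adjusted odds ratio.
- **Hospital stay:** time to discharge alive, with in-hospital death as a competing event. Name the hazard ratio (cause-specific or subdistribution) and show cumulative incidence of discharge by frailty. A time-to-discharge model that ignored death, or counted it as discharge, would keep the problem described above.
- **HDU/ICU days and intermediate-care days:** a two-part model (any or none, then duration) or negative binomial regression with its own effect measure. State how patients who die in the unit or before discharge are handled.
- **Change in independence:** state the coding, then the matching model.

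Limit the odds-ratio sentence to binary and ordinal outcomes, and settle the text before the data are analysed.

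The cost is a few lines of text and a little more analysis in standard software. Discharge and in-hospital death must be distinguishable in the dataset, which should be checked against the case report form. The drawback is that effect measures will differ between outcomes and need explaining in the report.

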### Anticipated recruitment

Data will be collected at participating sites for all patients meeting the inclusion criteria over a 3-month period. This has been calculated based on information submitted by participating sites regarding the number of laparotomies performed per month on patients aged ≥65 years. According to this, 3 months should permit the identification of 500 patients.

## Ethics and dissemination

### Ethical approval

Ethical approval for this study was granted by a National Health Service Research Ethics Committee via the Proportionate Review Service. This was granted by the Black Country Research Committee on 28 November 2016 (REC Reference 16/WM/0500). The same committee reviewed the amended protocol and granted a favourable opinion on6 February 2017.

### Registration

All participating units must obtain approval from their local Research & Development department consistent with the guidance from their relevant national organisation:. This study has been registered, reviewed and approved by the following organisations:The HRA (Health Research Authority) for sites in EnglandThe NRSPCC (NHS Research Scotland Permissions Co-ordinating Centre) for sites in ScotlandThe Health & Care Research Permissions Service for sites in Wales

The project will therefore be registered locally with the Trust Research & Development department prior to commencing patient identification and data collection at each site. It is the responsibility of the local ELF team to ensure that local Research and Development approvals are in place prior to commencing data collection.

